| Discontinuation criteria for each subject | The study will be discontinued for the subject who meets any of the following criteria.   1. The subject himself offered to withdraw from the study participation 2. The subject who could not comply with the prescribed administration of diclofenac sodium and study drug 3. The subject for whom the prescribed test was not performed 4. The subject who was judged impossible to move to the study period by the investigator, etc. 5. The subject who turned out that he did not meet the inclusion criteria or violated the exclusion criteria after the start of the study 6. The subject for whom the investigator, etc. judged that the study should be discontinued |
| Endpoints | [Efficacy endpoints]  Primary endpoint: Permeability of the small intestine using the lactulose/mannitol test  Secondary endpoints: endotoxin activity in blood, changes in intestinal flora  [Safety endpoints]  Adverse events, adverse reactions |
| Scheduled study period | May 2015 - March 2016 |

1. Background of this study

The results of the basic experiments suggest the correlation between small-intestinal mucosal injury and increase in the intestinal permeability and also the relationship with another disease recognized as Leaky Gut Syndrome.

Lubiprostone (brand name: Amitiza^®^ Capsules 24 µg (hereinafter referred to as the study drug) is a drug approved in November 2012 with “chronic constipation” as an indication. Since it is a prostaglandin derivative, it is reported from the basic experiments that the drug may prevent the onset of small-intestinal mucosal injury and increase in the intestinal permeability.

In this study, the effect of this study drug to contribute to the suppression of intestinal permeability will be examined by comparing the subjects in the study drug treatment group with those in the non-treatment group.

1. Objectives
   1. Primary objective

To evaluate permeability of the small intestine using the lactulose/mannitol test.

- 1. Secondary objectives

To evaluate endotoxin activity in blood.

To evaluate changes in the intestinal flora.

1. Subjects

The healthy adults who meet all of the following “3.1 Inclusion criteria” and do not correspond to any of the following “3.2 Exclusion criteria” will be the subjects in this study.

- 1. Inclusion criteria
     - 1. Men at age ≥20 years but <60 years when the consent was obtained

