- - - 1. Administer diclofenac sodium (75 mg/day) three times a day after every meal for 7 days.
      2. After administering diclofenac sodium for 7 days, the investigator, etc. will perform medical examination and allocate the subjects who can move to the study period to either a study drug treatment group or a control group.
      3. The lactulose/mannitol test, measurement of endotoxin activity in blood, and intestinal flora test will be performed.

For the first 6 subjects (3 subjects in each group) after the start of the study, the study treatment period or non-treatment period will be 28 days. For the 7th subject and after that, the study treatment period or non-treatment period will be determined to be either 14 days or 28 days based on the results of the 6 subjects.

[Up to the first 6 subjects]

[Study period]

(In the case of the study treatment group)

- - - 1. Administer 1 capsule of the study drug once a day after lunch for 14 days. The subjects are instructed to comply with the “Rules to be followed by subjects”.
      2. After administering the study drug for 14 days, the investigator, etc. will perform medical examination, as well as lactulose/mannitol test, measurement of endotoxin activity in blood, and intestinal flora test.
      3. Administer 1 capsule of the study drug once a day after lunch for 14 days.
      4. After administering the study drug for 14 days, the investigator, etc. will perform medical examination, as well as lactulose/mannitol test, measurement of endotoxin activity in blood, and intestinal flora test.

(In the case of the control group)

- - - 1. The study drug will not be administered (for 14 days). The subjects are instructed to comply with the “Rules to be followed by subjects”.
      2. After 14 days, the investigator, etc. will perform medical examination, as well as lactulose/mannitol test, measurement of endotoxin activity in blood, and intestinal flora test.
      3. The study drug will not be administered (for 14 days).
      4. After 14 days, the investigator, etc. will perform medical examination, as well as lactulose/mannitol test, measurement of endotoxin activity in blood, and intestinal flora test.

[After the 7th subject]

[Study period]

(In the case of the study treatment group)

- - - 1. Administer 1 capsule of the study drug once a day after lunch for 14 days or 28 days. The subjects are instructed to comply with the “Rules to be followed by subjects”.

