      2. After administering the study drug for 14 days or 28 days, the investigator, etc. will perform medical examination, as well as lactulose/mannitol test, measurement of endotoxin activity in blood, and intestinal flora test.

(In the case of the control group)

- - - 1. The study drug will not be administered (for 14 days or 28 days). The subjects are instructed to comply with the “Rules to be followed by subjects”.
      2. After administering the study drug for 14 days or 28 days, the investigator, etc. will perform medical examination, as well as lactulose/mannitol test, measurement of endotoxin activity in blood, and intestinal flora test.
  1. Study schedule

Screening period

Period for treatment with diclofenac

Period for treatment with study drug

At the time of discon-
tinuation

Informed consent

Medical examinations

Physical measurements (height/weight)

Vital signs

Enrollment

Allocation

Administer diclofenac

Confirmation of concomitant medications

Identification of adverse events

Administer the study drug

Lactulose/mannitol test

Serum endotoxin test

Intestinal flora test

Lactulose/mannitol test

Serum endotoxin test

Intestinal flora test

Not administer

All subjects

Study drug treatment group

Control group

⭘ Essential ◇ To be performed as far as possible

After 7th subject

Screening period

Period for treatment with diclofenac

Period for treatment with study drug

At the time of discontinuation

Informed consent

Medical examinations

Physical measurements (height/weight)

Vital signs

Enrollment

Allocation

Administer diclofenac

Confirmation of concomitant medications

Identification of adverse events

Administer the study drug

Lactulose/mannitol test

Serum endotoxin test

Intestinal flora test

Lactulose/mannitol test

Serum endotoxin test

Intestinal flora test

Not administer

All subjects

Study drug treatment group

Control group

Day (in the case of 14 days)^1)^

Day (in the case of 28 days)^1)^

⭘ Essential  ◇ To be performed as far as possible

1) Based on the results observed up to the 6th subject, a 14 day or 28 day treatment period of study drug (or non-treatment period) would be selected for the 7th subject and after that.

Up to the first 6 subjects

- 1. Matters to be followed by subjects

During the study period, the investigator, etc. or provides subjects with the following instructions. This study will be implemented according to the following procedures and schedules.

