- 1. Handling of personal data

For enrollment of a subject and preparation of his case report form, the investigator, etc. identify him by the subject identification code to retain the information as linkable anonymized data. Thus, personal data of a subject must be handled with caution.

1. Storage and destruction of records
   1. Storage of records

The investigator, etc. retains following records and documents for 5 years: case report forms, laboratory data, documents of ethical committee, documents on subject’s consent, documents on treatment with study drug and the study-related data.

- 1. Destruction of records

After completion of the storage period of records, the study-related data will be destroyed adequately, not to leak such secrets as personal data of subjects.

1. Statistical analysis

In this study, statistical analysis will be performed mainly for the following items. Details of the statistical design will be described in the statistical analysis plan.

- 1. Demographic characteristics

In addition to summary of subjects, summary statistics of demographic variables (including gender and age) of subjects will be shown.

- 1. Analysis set

Analysis set of the study will be Full analysis set (FAS) consisting of all subjects enrolled in the study, except for those described below.

• Subjects who were found to be ineligible for the study after the registration

• Subjects who took no study drug

• Subjects who had no efficacy data

- 1. Analysis methods for efficacy endpoints
     - 1. Primary endpoint

The summary statistics will be calculated for the permeability of the small intestine at baseline and after treatment respectively (mean, median).

For the primary analysis, (permeability of the small intestine after treatment - permeability of the small intestine at baseline) will be sought for each subject and the corresponding Wilcoxon test will be performed. The significance level will be 5% on both sides. For reference, the 2 groups will be compared using the Analysis of Covariance with permeability of the small intestine at baseline as a covariate.

- - - 1. Secondary endpoint

For endotoxin activities in blood and changes in the intestinal flora, too, (values after treatment - values at baseline) will be sought for each subject and the paired Wilcoxon test will be performed. The significance level will be 5% on both sides. For reference, the 2 groups will be compared using the Analysis of Covariance with baseline value as a covariate.

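### The only analysis set excludes anyone who took no study drug, which read literally removes the whole untreated control arm

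*Protocol*

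**What the plan says.** Protocol, Statistical analysis, Analysis set (22.2) names a single set: a "Full analysis set (FAS) consisting of all subjects enrolled in the study, except for those described below". Three exclusions follow: subjects found ineligible after registration, "Subjects who took no study drug", and subjects without efficacy data. None is restricted to one arm.

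The Background section says lubiprostone is "hereinafter referred to as the study drug". For the control group, Study procedures (8.2) states for the first six subjects "The study drug will not be administered (for 14 days", in two consecutive periods, and from the seventh subject on "The study drug will not be administered (for 14 days or 28 days".

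The next parts of the Statistical analysis section plan a comparison of the two groups by analysis of covariance, labelled as a reference analysis, for the primary and secondary endpoints. They also plan a comparison of adverse events and adverse reactions between the two groups.

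**The concern.** The trial exists to compare lubiprostone with no treatment, as the Background section says. An analysis set that keeps only those who took lubiprostone contains one arm, so the two-group analyses planned in the same section could not be run on it.

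Because the rule cannot be followed as it stands, someone has to reinterpret it. In an open-label trial with roughly 15 to 18 subjects per arm, that choice should not be left until data have been seen. The Statistical analysis section defers details to a statistical analysis plan, but the set itself is fixed in the protocol. A plan that copies the definition inherits the problem, and one that departs from it contradicts the protocol.

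**Working it through.** The protocol gives no figure to reproduce. The check is a reading of the definitions, followed by a head-count.

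**Reading 1: study drug means lubiprostone.**
- The Background section defines it so.
- Matters to be followed by subjects names diclofenac and study drug as two separate things.
- Compliance to study drug is collected in the treatment group only, while compliance to diclofenac is collected in both groups.
- Every control therefore meets the exclusion.

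Head-count on this reading. Inputs: the first block has size 6 with 3 per group (Study design; Method of allocation); later blocks have size 4. The allocation ratio in the later blocks is not stated, so 1:1 is assumed, as is no loss in the run-in. The protocol gives two sample sizes: 35 (Summary; Target sample size) and 30 (Design of sample size).

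| Total | After first 6 | Blocks of 4 | Controls | Controls left in the set |
|---|---|---|---|---|
| 30 | 24 | 6 complete | 3 + 6 × 2 = 15 | 0 |
| 35 | 29 | 7 complete, 1 left over | 3 + 7 × 2 = 17, or 18 if the last subject is a control | 0 |

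The share removed is 15/30 = 50%, or 17/35 = 49% to 18/35 = 51%. What remains is the lubiprostone arm alone.

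**Reading 2: study drug also covers diclofenac.**
- The Study drugs entries in the Summary and in Section 5 list both products.
- Expected adverse reactions of study drug uses the term for Voltaren.
- All subjects are scheduled to take diclofenac, so the controls stay in and the exclusion removes almost nobody.
- The base is still everyone enrolled. In Study procedures, registration comes first, then 7 days of diclofenac, then allocation of those able to continue. The termination criteria foresee subjects judged unable to move on. Such a subject has been enrolled, has taken diclofenac and has had a screening lactulose/mannitol test, but belongs to no group.
- Whether the third exclusion removes him depends on whether a screening value counts as efficacy data, which the section does not say.

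Neither reading defines the set as the subjects who were allocated.

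**The case against.** The strongest reply is that no sensible analyst would apply the line literally. Two-group comparisons are planned in the same section, and every efficacy measure is collected in the control group. That stands: this is a drafting error, and the counts above show what the words say, not a loss to be expected.

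It is also fair that the definition is not used consistently. Besides the places where the term covers diclofenac, the control-group step from the seventh subject on times the assessment from administration of the study drug, which conflicts with the step before it and needs to be reconciled. This weakens the claim that only one reading is possible. It does not defend the wording, since the one explicit definition is lubiprostone.

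Three stronger readings are tempting and are not supported.
- A reader might infer that no efficacy analysis could be run. The primary test is a Wilcoxon test on each subject's change from baseline, and the parallel secondary text calls it paired. A within-subject test could still be run in the lubiprostone arm. What is lost is the comparison between groups.
- A reader might infer that, on the wider reading, never-allocated subjects would contaminate the comparison. They have no group and no value after treatment, so they cannot enter the analysis of covariance, and the exclusion for missing efficacy data may remove them anyway. The fault is in how the set is defined.
- A reader might infer that the trial will be biased by applying the exclusion to the lubiprostone arm only. The protocol does not propose this, and nothing in it indicates how many allocated subjects would never start.

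**Conclusion.** The point holds as a defect of wording with a real consequence. By the protocol's own definition of study drug, the only analysis set contains no controls: 15 of 30 subjects removed, or 17 to 18 of 35, given 1:1 allocation in the blocks of 4 and no run-in loss. This contradicts the planned two-group analysis of covariance and safety comparison. The result is plainly unintended. If the term is read to include diclofenac the controls return, but a base of enrolled subjects is still not the allocated population. The definition should be corrected before any analysis. It does not show that the primary within-subject test is impossible or that any result would be biased.

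**What to change.** In Analysis set (22.2):
1. Define the full analysis set as all allocated (randomised) subjects, analysed in the group to which they were allocated.
2. Delete the exclusion of subjects who took no study drug, so that both arms follow the same rule. Restricting it to the lubiprostone arm would drop allocated subjects who never start, with no counterpart among controls.
3. Keep the requirement for efficacy data, but state that it means data after allocation, applied identically in both arms. Study procedures lists the tests at the end of the diclofenac period after the allocation step, so say explicitly that a measurement from the treatment or non-treatment period is meant.
4. Use study drug in one sense throughout, and reconcile the control-group step noted above.

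Adverse events are collected from the start of diclofenac. Those arising before allocation should stay reported separately and should not disappear with the narrower set.

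The cost is a few sentences in the protocol, carried into the statistical analysis plan. No subjects, visits or data are added. The change does not restore values for subjects who stop early, because tests after discontinuation are not done as a rule.

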4.3.3　　At revision of the informed consent form

If the informed consent form is revised, the investigator, etc. should obtain the subject’s consent again.

1. Study drugs

Voltaren^®^ Tablets 25 mg (containing 25 mg of diclofenac sodium in 1 tablet)

Amitiza^®^ Capsules 24 µg (containing 24 µg of lubiprostone in 1 capsule)

1. Study design
   1. Study design

Open-label, randomized, parallel-group comparison study

For the first 6 subjects (3 subjects in each group) after the start of the study, the study treatment period or non-treatment period will be 28 days in this study. For the 7th subject and after that, the study treatment period or non-treatment period will be determined to be either 14 days or 28 days based on the results of the 6 subjects. If there is no difference in the 14-day treatment between the two groups but it is judged that there may be a tendency of difference in the 28-day treatment between the two groups, the study treatment period will be determined to be 28 days for the 7th subject and after that. In other cases, the study treatment period will be determined to be 14 days for the 7th subject and after that.

- 1. Dosage and administration of the study drug

Subjects will orally receive one capsule of Amitiza once daily after lunch for 14 days or 28 days.

- 1. Study registration

**This study will be registered to the UMIN Clinical Trials Registry and the information on the study will be made public. The clinical study registration will be done before registration of the first subject.**

- 1. Target sample size

35 subjects

- 1. Flow chart

*1: Lactulose/mannitol test, measurement of endotoxin activity in blood, intestinal flora test

*2: For the 7th subject and after that, the study treatment period (non-treatment period) will be determined to be either 14 days or 28 days based on the results of the first 6 subjects (3 subjects in each group).

Visit (1)

Visit (2)

Visit (3)

Study drug treatment group

Control group

Explain and obtain the consent

Medical examination, physical findings, etc.

Case registration

Administer diclofenac

Allocation

Tests for intestinal permeability^*1^

Tests for intestinal permeability^*1^

Administer the study drug

Not administer

←14 or 28 days*^2^→

7 days

←14 or 28 days*^2^→

Tests for intestinal permeability^*1^

Up to the first 6 subjects

Visit (1)

Visit (2)

Visit (3)

Visit (4)

Study drug treatment group

Control group

Explain and obtain the consent

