Medical examination, physical findings, etc.

Case registration

Tests for intestinal permeability^*1^

Administer diclofenac

Allocation

Tests for intestinal permeability^*1^

Administer the study drug

Not administer

Tests for intestinal permeability^*1^

Tests for intestinal permeability^*1^

Administer the study drug

Not administer

14 days

14 days

14 days

14 days

7 days

*1: Lactulose/mannitol test, measurement of endotoxin activity in blood, intestinal flora test

After 7th subject

- 1. Method of allocation

Until the 6th subject, block randomization is conducted using a block of block size 6. For the 7th subject and after that, block randomization is conducted using a block of block size 4.

- 1. Prohibited concomitant medications and therapies

After obtaining the consent until the completion of the study period, the use of proton pump inhibitors (PPIs), antibiotics, and intestinal drugs will be prohibited. However, the use of antibiotics will be allowed only for a local therapeutic purpose.

If the prohibited medication is used for inevitable reasons such as the treatment of adverse events, the investigator, etc. should describe the drug name, duration of use, intended use, etc. in the case report form.

1. Study implementation period

May 2015 - March 2016

1. Study method

This study will be implemented according to the following procedures and schedules.

- 1. Recruitment of subjects

The outline of this study will be posted on a bulletin board, etc. in the university to recruit subjects.

- 1. Study procedures

For the first 6 subjects (3 subjects in each group), the study treatment period or non-treatment period will be 28 days in this study. For the 7th subject and after that, the study treatment period or non-treatment period will be determined to be either 14 days or 28 days based on the results of the 6 subjects.

[Acquisition of consent]

- - - 1. The investigator, etc. will explain the contents of this study using the information document and obtain the written consent.
      2. After obtaining the consent, the investigator, etc. will perform medical interview, body measurements, etc. to judge the appropriateness of the subject’s participation.
      3. If the subject was judged to be eligible for participation, the subject will be registered. Also, the lactulose/mannitol test, measurement of endotoxin activity in blood, and intestinal flora test will be performed.

[Increase of intestinal permeability]

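### The reference two-group ANCOVAs adjust for baseline but not for allocation stage (first six subjects versus 7th onward), a small avoidable loss of precision if the stages differ

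*Protocol*

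**What the plan says.** **Allocation (Protocol, Method of allocation).** "Until the 6th subject, block randomization is conducted using a block of block size 6". Then: "For the 7th subject and after that, block randomization is conducted using a block of block size 4". The Study design section gives the split of the first block: "For the first 6 subjects (3 subjects in each group) after the start of the study".

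**Schedule (Protocol, Study design and Study procedures).** The first six have a fixed 28-day period. They are tested midway ("After administering the study drug for 14 days, the investigator, etc. will perform medical examination, as well as lactulose/mannitol test") and again after a further 14 days. Their results decide whether later subjects have 14 or 28 days, and 14 is the default. Later subjects have one test, at the end of the chosen period.

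**Analysis (Protocol, Analysis methods for efficacy endpoints).** For the primary endpoint, the change from baseline "will be sought for each subject and the corresponding Wilcoxon test will be performed". The group comparison follows, labelled as for reference: "the 2 groups will be compared using the Analysis of Covariance with permeability of the small intestine at baseline as a covariate". For endotoxin activity and intestinal flora the Wilcoxon test is described as paired, and again for reference "the 2 groups will be compared using the Analysis of Covariance with baseline value as a covariate". Stage is not mentioned. The section leaves details of the statistical design to the SAP, which is not at hand.

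**The concern.** The first six subjects form a separate allocation stage. Their 3:3 balance is forced within their own block, their schedule differs, and they must be assessed before the later duration can be set. The usual principle is to analyse in line with how subjects were randomised, and the stated model does not.

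The protocol itself offers a way for the stages to differ. It does not say which day counts as after treatment for the first six. If it means the end of treatment and later subjects have 14 days, the first six are measured 28 days after the diclofenac week and the rest 14 days after it. Since permeability has been raised deliberately, a shift with time since the challenge is plausible.

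Precision of the group difference is at stake. If the Wilcoxon tests are within-group, as the word paired suggests for the secondary endpoints, these ANCOVAs are the only stated efficacy analyses that compare the groups. That comparison is the aim given in the Background.

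**Working it through.** The protocol gives no effect size, SD, power or precision target, so there is no planned figure to reproduce. The check asks what omitting stage costs over a range of assumed stage differences.

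**Inputs from the protocol**
- Stage 1: 6 subjects, 3 per group. Stage 2: blocks of 4.
- N: 30 (Design of sample size) or 35 (Target sample size). Both are shown.
- Two-sided 5% level.

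**Assumptions**
- Blocks of 4 split 2:2 (the ratio is not stated).
- Stage difference d, in residual SDs, from 0 to 2.
- Treatment effect of 1 residual SD for power.
- Baseline moderately predictive of outcome (slope 0.5 on a standardised baseline).

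**Closed form.** Let p = 6/N be the stage 1 fraction. With arms balanced within stage, the true variability of the estimated group difference does not depend on d, but the estimated residual variance does. Omitting stage multiplies the standard error by √(1 + p(1−p)d²).

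- N = 30: p = 0.20, p(1−p) = 0.16. For d = 0.5, √1.04 = 1.020; for d = 1, √1.16 = 1.077.
- N = 35: p = 0.171, p(1−p) = 0.142. For d = 0.5, √1.0355 = 1.018; for d = 1, √1.142 = 1.069.

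The effective critical value rises by the same factor. For N = 30 and d = 1 it is 1.96 × 1.077 = 2.11, which gives a two-sided normal tail of about 3.5%.

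**Simulation.** 6,000 trials per setting: one block of 6 then blocks of 4, comparing ANCOVA on baseline with ANCOVA on baseline and stage. The shift is in the post-treatment value only.

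| d (residual SD) | CI width ratio without/with stage, N=30 | Same, N=35 | Type I error without stage, N=30 | Power without / with stage, N=30 |
|---|---|---|---|---|
| 0 | 0.998 | 0.998 | 0.045 | 0.741 / 0.738 |
| 0.5 | 1.019 | 1.017 | 0.048 | 0.724 / 0.737 |
| 1 | 1.080 | 1.071 | 0.035 | 0.674 / 0.728 |
| 1.5 | 1.174 | 1.155 | 0.024 | 0.607 / 0.739 |
| 2 | 1.298 | 1.265 | 0.013 | 0.521 / 0.734 |

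A second set of 6,000 trials gave 1.079 and a type I error of 0.034 at d = 1, N = 30. With the stage term, type I error stayed near 5%. Bias was negligible with and without the term.

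**Cost of the term when d = 0.** Residual degrees of freedom fall from 27 to 26 at N = 30. The t quantiles are 2.0518 and 2.0555, ratio 0.998, so the interval widens by about 0.2%.

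**If the shift also appears in baseline.** An assay-batch or early-entrant effect could move both values, and the covariate then absorbs much of it. With the same shift in both (correlation 0.5, N = 30), omitting stage widens the interval by at most about 0.3%, 1.5%, 3.1% and 4.8% for shifts of 0.5, 1, 1.5 and 2 SD. Type I error stays between about 4% and 5%.

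**The case against.** The strongest case against has four parts.

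- **The target is a supplementary analysis in a pilot.** The ANCOVA is labelled as for reference, and the primary analysis is a Wilcoxon test on change. This stands, and it keeps the point minor. It does not remove it, because these ANCOVAs may be the only efficacy analyses that compare the groups.
- **Extra model terms belong in the SAP.** Naming baseline does not rule out a further factor, and the SAP may already include stage. This stands as a limit. The protocol's wording still names baseline alone.
- **The stages may hardly differ.** The first six have a day-14 value obtained after the same screening test, diclofenac week, post-diclofenac test and 14-day course as later subjects on 14 days. The second 14 days comes after that value and cannot affect it. If 28 days is chosen, the procedural difference is one intermediate test. What remains is calendar time and possible assay batch, and the documents report no shift from either. This largely stands. It depends on the matching day being used, which the analysis section does not say.
- **A change of block size alone is not a stratification factor.** True. The reason for a stage term is the closed first block together with its own schedule and earlier assessment.

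A reader might infer that the comparison is too imprecise, that its standard error is simply wrong, or that the 5% level is exceeded. The documents support none of these. No precision target exists to be missed, the standard error is inflated only if an unexplained stage difference exists, and the type I error then falls below 5%. Losses above 15% need a stage difference of about 1.5 SD, which nothing in the protocol suggests.

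**Conclusion.** The point holds as a minor, conditional improvement. The stated two-group ANCOVAs do not reflect the stage in which subjects are allocated. Omitting stage does not itself bias the estimate. If the stages differ beyond what baseline explains, it makes the interval avoidably wide and the test conservative. At N = 30 the widening is about 2% for 0.5 SD and about 8% for 1 SD; the latter brings a type I error near 3.4% and, for an assumed 1-SD effect, about 5 points less power. At N = 35 the widening is slightly smaller. It is smaller again if the shift shows in baseline.

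These sizes rest on an assumed stage difference, a 2:2 split in the later blocks and the baseline relation used. The case for acting is the asymmetry: about 0.2% in width if the stages do not differ, against a modest gain if they do.

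**What to change.** In the analysis section or the SAP, add stage (first six subjects versus 7th subject onward) as a fixed factor beside the baseline value in each two-group ANCOVA, for permeability, endotoxin activity and intestinal flora. If any rank test is used between the groups, stratify it by the same factor (van Elteren).

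The cost is one model term and one degree of freedom, with no new data or visits. The term does not settle which day's value from the first six enters the analysis, nor does it deal with the use of their results to choose the later duration. Those are separate matters.
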